AEs of special interest are required to immediately report to the sponsor. Sponsor is responsible for addressing potential new risks of clinical trial by appropriate approaches. Investigators are required to immediately report these following events to the sponsor. In all cases, investigators are required to report the event to the sponsor within 24 hours after learning of the event. Details events (regardless of its causality to study drug) are listed as following:

(1) Pregnancy in female subjects

Female subjects of childbearing potential are recommended to notify the investigators immediately if pregnancy was confirmed during the study or within 6 months after the last dose of study drug. Investigator(s) are required to complete the Clinical Trial Pregnancy Report Form and report to the sponsor or their designated personnel within 24 hours of being informed of a pregnancy occurrence and submit it to the sponsor or their designated personnel. Pregnancy events should not be documented in the electronic Case Report Form (eCRF) of AEs. Investigator should discontinue the treatment for pregnant subjects, provide advices, and discuss the risks of continuing the pregnancy and potential impacts on the fetus. Pregnant subjects will be monitored until the end of pregnancy. Investigator is required to submit the Clinical Trial Pregnancy Report Form when obtaining the latest information on the pregnancy process and outcomes.

(2) Pregnancy in female partner of the male subjects

Male subjects were informed by the informed consent that if their partner pregnant during the study period or within 6 months after the last dose of study drug, they should immediately notify the investigator. Investigator(s) are required to complete the Clinical Trial Pregnancy Report Form and report to the sponsor or their designated personnel within 24 hours of being informed of a pregnancy occurrence and submit it to the sponsor or their designated personnel. Investigator should provide advices, and discuss the risks of continuing the pregnancy and potential impacts on the fetus, meanwhile, discuss with her primary physician and/or obstetrician to discuss reasonable solutions. If subjects decide to continue the pregnancy, the investigator should collect detailed information about the course and outcome of the pregnancy in detail. Meanwhile, partners with pregnancy needs to sign an authorization form, allowing the use and disclosure of the health information related to this pregnancy and agreeing to undergo subsequent follow-ups for the pregnancy. After signing authorization, investigator is required to submit the Clinical Trial Pregnancy Report Form when obtaining the latest information on the pregnancy process and outcomes.

(3) Spontaneous abortion

Spontaneous abortion should be reported as SAEs (abortion has great significant significance assessed by sponsor) and recorded in the eCRF. Investigator(s) is required to report the SAE after aware of the occurrence of spontaneous abortion, as per the procedure in 6.4.3 section.

(4) Congenital anomalies/birth defects

Any congenital anomalies/birth defects in infants born to female subjects or female partners of male subjects who had taken study drugs should be reported as SAEs in the eCRF. Investigator(s) is required to report the SAE after aware of the occurrence of congenital malformations/birth defects, as per the procedure in 6.4.3 section.

- - 1. Management of common AEs

**6.5.6.1 Common AEs related to TQB2450**

Types and treatment recommendations of immune-related adverse events (irAEs) caused by TQB2450 are listed in Appendix 6.

**6.5.6.2 Common AEs related to Anlotinib**

**(1)** **Hand-foot skin reaction (HFSR)**

HFSR is a disease characterized by redness, marked discomfort, swelling and tingling of the palms or soles of the feet. It usually occurs in subjects treated with chemotherapy or targeted therapy

Grade 1: Minimal skin changes or dermatitis (e.g., localized erythema, hyperkeratosis, oedema) and painless;

Grade 2: Significant skin changes (flaking, blisters, swelling, and hyperkeratosis) and pain, interfering with daily life and activities.

Grade 3: Severe skin changes (flaking, blisters, bleeding, ulcers, oedema, and hyperkeratosis) with significant pain and limited personal self-care ability.

For subjects occurred grade 1 HFSR, supportive treatment is not required. For subjects occurred ≥grade 2 HFSR, the following supportive treatments are recommended: strengthen skin care, keep skin clean, avoid secondary infection; avoid pressure or friction; use moisturizers or lubricants, and topically apply lotions or lubricants containing urea and corticosteroids; topical antifungal or antibiotic therapy when necessary.

**(2)** **Hypertension**

In previous studies, anlotinib is associated with the frequent occurrence of hypertension and the incidence of grade 3 or higher hypertension was 13.61%. During this study, subjects are recommended to monitor blood pressure during treatment. In the event of a hypertensive event, the following managements are recommended:

Grade 1: Pre-hypertension (systolic blood pressure [SBP] 120-139 mmHg or diastolic blood pressure [DBP] 80-89 mmHg); No indication for antihypertensive drugs and blood pressure is monitored.

Grade 2: Stage 1 hypertension (SBP 140-159 mmHg or DBP 90-99g mmHg); Medical intervention is required. For recurrent or persistent (≥24 hours), symptomatic hypertension with >20mmHg SBP increases or >140/90 mmHg increase of previously normal range, monotherapy and blood pressure monitoring are required. Thiazide diuretic, angiotensin-converting enzyme inhibitors (ACEI), angiotensin II receptor blockers (ARB), beta-blocker, or calcium-channel blocker are commonly used.

Grade 3: Stage 2 hypertension (SBP ≥160 mmHg or DBP ≥100 mmHg); Medical intervention is required. Multidrug therapy is required, commonly using a thiazide diuretic combined with an ACEI, beta-blocker, or calcium-channel blocker.

Grade 4: Life-threatening (e.g., malignant hypertension, persistent neurological deficit, hypertensive crisis). Urgent treatments are required.

Hypertension emergencies: SBP >120 mmHg accompanied by acute or progressive target organ damage (e.g., Cerebral infarction, intracranial or subarachnoid hemorrhage, hypertensive encephalopathy, etc.); among them, the progressive or rapidly progressive hypertension based on chronic essential hypertension is the most common (about 40%-50%).

Hypertension urgencies: SBP >120 mmHg with no or minor organ damage.

In case of hypertensive crisis, subjects should discontinue the study treatment and withdraw from the study.

When subjects occur elevated blood pressure during vital sign measurements, a second measurement should be taken after a 15-minute rest. If the elevation is repeated and reaches the grade 2, it can be defined as an AE of hypertension. If the time of improvement from the first occurrence of hypertension to its reappearance is less than 1 week, it is identified as one AE and record the highest level of severity. The start time is defined as the time of the first hypertensive episode, and the end time is defined as the last outcome time of hypertension.

**(3) Proteinuria**

Proteinuria should be monitored closely for all subjects during the treatment period, particularly for subjects with a history of hypertension. For subjects with 2 consecutive results of urine protein (++), 24-hour urinary protein measurement should be performed. For subjects experienced proteinuria, doses are adjusted as per the principles listed in the dose adjustment section of the protocol.

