5. Physical examination: Whole body system examination (facial features, integumentary system, lymph nodes, eyes, ears, nose, throat, abdomen, spine, extremities, and nervous system) are performed within 7 days before enrollment, at C1D7, C1D21, and thereafter at days 21 of every two cycles (odd numbered cycles), and at dropout visit;
6. Vital signs: Temperature, pulse rate, and respiratory rate are performed within 7 days before enrollment, at C1D7, C1D21, and thereafter at days 21 of every two cycles (odd numbered cycles), and at dropout visit; Blood pressure monitoring is described in [22];
7. Medical history: Pathological results, EGFR T790M mutation test report; history of tumor surgery, chemotherapy, radiotherapy, and other disease treatment;
8. Compliance before enrollment: Days between the first progression of the subject and enrollment;
9. Hemanalysis: Hemoglobin, red blood cells, white blood cells, neutrophil count, lymphocyte count, and platelets count are performed within 7 days before enrollment, at C1D7, C1D21, and thereafter at days 21 of every two cycles (odd numbered cycles), and at dropout visit, and at days 21 after treatment. If the neutrophil count ≤1×109/L or platelets (PLT) ≤50×109/L, additional examination (1 time/2-3 days) is required; weekly hemanalysis is required if there is a delay in dosing or dose adjustment due to hematological toxicity;
10. Urinalysis: Urine protein, glucose, occult blood (red blood cell and white blood cell), pH, and ketone bodies are performed within 7 days before enrollment, at C1D7, C1D21, and thereafter at days 21 of every two cycles (odd numbered cycles), and at dropout visit, and at days 21 after treatment; If the semi-quantitative method shows the levels of protein ≥2+ (e.g., urine test strip), 24-hour urine protein quantification should be performed;
11. Stool tests: Occult blood test is performed within 7 days before enrollment, at C1D7, C1D21, and thereafter at days 21 of every two cycles (odd numbered cycles), and at dropout visit.

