**Table 5.5-5 Dose adjustments related to anlotinib hydrochloride capsules- proteinuria**

| Grade of AEs | Definition | Recommended actions | Adjustment of administration regimens |
| --- | --- | --- | --- |
| Grade 1 | Proteinuria 1+, or urinary protein < 1.0g/24 hours | Planned visits | Maintain the original dose |
| Grade 2 | Proteinuria 2+, and urinary protein < 1.0g/24 hours | Planned visits | Maintain the original dose |
|  | Proteinuria 2+, and urinary protein 1.0-3.4g/24 hours | Delayed dosing and medical intervention treatment until proteinuria ≤ 2+ and urinary protein < 1.0g/24 hours | Maintain the original dose |
| Grade 3 | Urinary protein≥3.5g/24hours | Delayed dosing and medical intervention treatment until proteinuria ≤ 2+ and urinary protein < 1.0g/24 hours | reduce 1 dose level |

1. Bleeding events (including hemoptysis, gastrointestinal bleeding, epistaxis, bronchial bleeding, gingival bleeding, gross hematuria, fecal occult blood, and cerebral hemorrhage).

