Systematic physical examination, ECOG performance status and vital signs are required to be performed within 7 days before enrollment. Results within±7 days of study completion/withdrawal are allowed at the last visit. Reexamination is required if the examinations are outside the acceptable time window.

All vital signs should be measured in a resting state. If body temperature is measured more than twice in a day, the highest result is recorded.

Blood pressure monitoring: Blood pressure is monitored by the subject himself/herself recorded in the patient diary card. Blood pressure is monitored on alternate days for the first 4 weeks of treatment, at least every 1 week from week 5 to week 12, and at least every 4 weeks thereafter. If blood pressure is abnormal, it should be monitored daily; if blood pressure is normal, normal monitoring frequency can be resumed. Blood pressure is re-measured by investigator at each visit.

- - 1. Laboratory examination

| **Table 6.2-1 6.2.2 Laboratory examination** | |
| --- | --- |
| **Categories** | **Items** |
| Hemanalysis | WBC, ANC, lymphocyte count, red blood cells, Hb, platelet count |
| Urinalysis | red blood cell, white blood cell, and urine protein (analysis of 24-hour urine protein will be performed if necessary) |
| Stool tests | white blood cell, red blood cell, and occult blood |
| Blood biochemistry | ALT, AST, GGT, AKP, TP, ALB, TBIL, DBIL, GLU, BUN/Urea, Cr, UA, K^+^, Na^+^, Cl^-^, Ca^2+^, Mg^2+^, P, LDH, TC, TG, HDL, LDL |
| Coagulation function | INR, APTT, PT, FIB |
| Thyroid function | FT3, FT4, TSH |
| Lipase | Serum lipase (as appropriate) |
| Amylase | Serum amylase (as appropriate) |
| Tumor markers | Serum carcinoembryonic antigen (CEA) |
| Pregnancy | Serum HCG/urineHCG |
| Epidemiology | HbsAg (HBV DNA test for positive HbsAg), HBsAb, HBeAg, HBeAb, HBcAb, Anti-HCV, HIV |

During the screening period, the laboratory tests within 7 days before enrollment are allowed. Results within ±7 days of study completion/withdrawal are allowed at the last visit. Re-examination is required to comply with the requirements of the clinical study if the examinations are outside the acceptable time window.

- - 1. Cardiac function examination

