| Urinalysis | urine RBC, urine WBC, proteinuria, glucose in urine (proteinuria ≥ 2+, additional 24-h urine protein quantification is required within 1 week) |
| Stool tests | leukocyte, RBC, occult blood |
| Blood biochemistry | ALT, AST, GGT, ALP, LDH, TP, ALB, TBIL, DBIL, GLU, BUN/Urea, Cr, K^+^, Na^+^, Cl^-^, Ca^2+^, Mg^2+^, P, TC, TG, HDL, LDL |
| Six coagulation tests | INR, APTT, PT, FIB, TT, D-D dimer |
| Lipase | lipase |
| Amylase | amylase |
| Tumor marker | carcinoembryonic antigen |
| Pregnancy text | human chorionic gonadotophin |
| Epidemiological | HbsAgn (Additional HBV DNA if positive), HBsAb, HBeAg, HBeAb, HBcAb, Anti-HCV, HIV |

- - - 1. **Physical examination**

The physical examination was classified according to normal and abnormal, and the cross-classification table was used. Frequency and percentage were used to summarize the physical examination descriptively.

- - - 1. **Vital signs**

Means, standard deviations, medians, quartiles, and minimum and maximum values will be listed for vital signs, describing the measurements and changes before and after treatment. Paired *t* tests were performed when necessary.

- - - 1. **12-lead electrocardiogram**

The 12-lead electrocardiogram was classified according to clinical significance, namely normal, abnormal without clinical significance, abnormal with clinical significance or normal and abnormal. The 12-lead electrocardiogram was summarized descriptively by frequency and percentage using cross-classification table.

- - - 1. **Concomitant medications**

The WHODrug was used to code the combined drugs, and the use of combined drugs during the study period and the frequency of each drug were summarized. The details of the combined drugs are listed.

- - 1. **Efficacy analysis**
       1. **Analysis of primary efficacy endpoints**

PFS is defined as the time from enrollment to the first time of disease progression or death from any cause, whichever occurs first.

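### The proteinuria management section triggers 24-hour urine protein after two consecutive ++ results, but the schedule footnote and laboratory table trigger it at any result of 2+ or more, and the dose table needs the value at 2+

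*Protocol*

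**What the plan says.** Three places in the protocol state when a dipstick result leads to a 24-hour collection.

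- Section 6.5.6.2 (3), on managing proteinuria as an adverse event: "For subjects with 2 consecutive results of urine protein (++), 24-hour urinary protein measurement should be performed". Its next sentence hands dosing to another section: "For subjects experienced proteinuria, doses are adjusted as per the principles listed in the dose adjustment section of the protocol".
- Footnote 10 (urinalysis) to the visit schedule, printed under Study Procedures and again under the stage 2 flow chart in section 6.1: "If the semi-quantitative method shows the levels of protein ≥2+ (e.g., urine test strip), 24-hour urine protein quantification should be performed". It asks for no repeat result and gives no time limit.
- The laboratory table in section 8.2.5: "proteinuria ≥ 2+, additional 24-h urine protein quantification is required within 1 week". It asks for no repeat either, and it is the only place with a time limit.

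The dose rules are in Table 5.5-5. A 2+ dipstick is split by the 24-hour value. The row "Proteinuria 2+, and urinary protein < 1.0g/24 hours" keeps the dose and planned visits. The row "Proteinuria 2+, and urinary protein 1.0-3.4g/24 hours" delays dosing. Grade 3 is defined by the 24-hour value alone, "Urinary protein≥3.5g/24hours", and leads to a delay and a reduction of one dose level.

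The protocol does not say which trigger governs.

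**The concern.** The section a clinician would consult for this adverse event states a later trigger than the schedule footnote does. It then relies on a dose table whose deciding input it has not yet called for. A patient with a first 2+ may already excrete 1.0 g or more in 24 hours, where the table delays anlotinib, or 3.5 g or more, where it also reduces the dose. Under the two-result trigger that would not yet be known, and the patient could stay on the unreduced dose. A site working from footnote 10 would test after the first result. At stake are dosing safety in individual patients and consistency between sites in when proteinuria is quantified and acted on.

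**Working it through.** The protocol states no figure to reproduce. The check compares the rules and then counts days between scheduled urinalyses.

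**Rules applied to a first 2+ result**

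| Source | 24-hour test called for at the first 2+? | Time limit |
| --- | --- | --- |
| Section 6.5.6.2 (3) | No, after a second consecutive ++ | None |
| Footnote 10 (both schedules) | Yes | None |
| Section 8.2.5 laboratory table | Yes | 1 week |
| Table 5.5-5 | Sets no trigger, but needs the value to choose a row | None |

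The pre-cycle criteria in section 5.5 (Criteria for Dose Delay) do not close the gap. They allow a cycle to start with proteinuria up to and including 2+ and name no 24-hour value. A patient at 2+ with 1.0 g or more in 24 hours passes that line.

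**Inputs for the interval.** Urinalysis is at C1D7, C1D21, then day 21 of odd-numbered cycles, with a window of ±3 days per visit (visit schedule and footnote 10). A cycle is 21 days. Anlotinib is given for 2 weeks, then stopped for 1 week (section 5.5, Administration principles).

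**Days from first to second scheduled result**

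- C1D7 to C1D21: 21 − 7 = 14 days. With opposite ends of both windows, 14 ± 6 gives 8 to 20 days.
- C1D21 to C3D21, and each later pair: 2 × 21 = 42 days. With windows, 42 ± 6 gives 36 to 48 days.
- Against the 1-week limit, on nominal days: 14 − 7 = 7 and 42 − 7 = 35 days longer.

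**Why this does not convert to a fixed number of doses**

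- First 2+ at C1D7: doses before C1D21 fall on days 8-14, which is 7. The 1-week limit also ends on day 14, so it too allows 7. On nominal days the excess is 7 − 7 = 0 doses, because the extra week is off drug.
- First 2+ at C1D21, second result only at C3D21: two dosing periods, 2 × 14 = 28 doses. The 1-week limit allows C2D1-7, which is 7.
- First 2+ at C1D21, with that sample also serving as the check for cycle 2 and the next check before C3D1: 14 doses.
- First 2+ at C1D21, with a separate check before C2D1: 0 doses, because no anlotinib is given in between.
- A repeat dipstick soon after the first result, which section 6.5.6.2 (3) permits, also brings the excess to 0.

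The count runs from no excess to 28 − 7 = 21 doses, depending on site practice that the protocol does not fix.

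**The case against.** The strongest reply is that the rules are compatible. Section 6.5.6.2 (3) does not restrict the test to patients with two results and does not tell a site to wait. It also asks for close monitoring of urine protein. A site that tests at the first 2+, as the schedule footnote says, complies with everything. The cross-reference to the dose rules even prompts earlier testing, since Table 5.5-5 cannot be read at 2+ without the value. All of this stands, and it limits the point. A reader might infer that the protocol cannot be followed, and the text does not support that.

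It does not remove the point. To reach the compliant path a site must find all the rules and choose the strictest. The section on this adverse event gives the latest trigger, and the only time limit is in a table in the statistical section. A two-result trigger could be a reasonable choice by itself, but it does not fit beside two single-result triggers and a dose table that needs the value at once.

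Two other stronger readings fail. A reader might infer that some minimum number of doses must be given without the deciding value; the count above reaches zero under practices the protocol allows. A reader might also take the entry in Table 6.2-1, "analysis of 24-hour urine protein will be performed if necessary", as a further conflicting trigger. It is an item in a list of assays, and footnote 10 supplies the trigger.

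**Conclusion.** The point holds as a minor inconsistency in dosing safety and between sites. Section 6.5.6.2 (3) states a later trigger than footnote 10 and section 8.2.5, and later than Table 5.5-5 needs. The size is a possible 14 or 42 nominal days without the deciding value, against 7 days in section 8.2.5. It rests on two assumptions: that a site treats section 6.5.6.2 (3) as the operative trigger, and that it waits for the next scheduled urinalysis. If either fails, the excess shrinks and may vanish. The documents do not show how many patients would have a first 2+ with 1.0 g or more in 24 hours, so no frequency is claimed. Sample size, power and the primary analysis are unaffected.

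**What to change.** Replace the two-result sentence in section 6.5.6.2 (3) with: any urine protein result of 2+ or more requires 24-hour urinary protein quantification within 1 week. This matches the trigger in footnote 10 and both the trigger and the time limit in section 8.2.5, which can stay as they are.

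Three further edits are optional: repeat the same trigger in Table 6.2-1, add a reference to Table 5.5-5 in the proteinuria line of the dose-delay criteria, and extend the table's 1.0-3.4 g row from 2+ to 2+ or more.

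The cost is one sentence in a protocol amendment. Footnote 10 already requires the collections, so the change adds no testing beyond what the schedule asks for.

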**(4)** **Diarrhea**

Grade 1 to 2 diarrhea could be treated with supportive care at the onset (e.g., 4 mg loperamide orally followed by 2 mg every 2 hours until diarrhea is resolved).

**(5) Hyperlipidemia**

The management of hyperlipidemia should consider the patient's pre-treatment state and dietary habits. In addition to dietary control, hypercholesterolemia of grade 2 or higher (≥7.75 mmol/l) or hypertriglyceridemia of grade 2 or higher (≥2.5 times×UNL) should be treated with HMG-CoA reductase inhibitors (atorvastatin, etc.) or appropriate lipid-lowering agents.

**(6) Gastrointestinal bleeding**

The presence of gastrointestinal bleeding, including fecal occult blood (++) and above, vomiting blood, or fresh blood in the stool, should be treated actively and symptomatically. For upper gastrointestinal bleeding, fasting should be performed and treatment consisting of anti-acid, gastric mucosa protection, anti-bleeding (hemostatic cyclic acid, reptilase, etc.) and, if necessary, octreotide should be administered; for lower gastrointestinal bleeding, anti-bleeding, blood transfusion and supportive treatment should be given; for uncontrolled bleeding, assistance from a surgeon is required immediately.

**(7) Thyroid dysfunction**

The thyroid function should be monitored closely for all subjects. Symptomatic treatments (e.g., Euthyrox) are required when TSH ≥20 mU/L or any value of T3, T4, FT3, and FT4 is lower than the normal value. During the study period, if thyroid dysfunction is considered as an AE by the investigator, the beginning time of AE is defined as the time of the first laboratory abnormality of thyroid function.

1. **Data management and statistical analysis**
   1. **Data entry**

The data collected in this study will be conducted using the electronic data capture (EDC) system. Investigator(s) or designated representative should complete the source document/eCRF timely, accurately, completely, and normatively. Data entry must be performed by authorized personnel who are qualified in EDC operation training.

- 1. **Data verification**

Clinical research associates (CRA) have to conduct the source data verification to ensure the accuracy, completeness, consistency, and standardization of the data. Data administrators have to verify the data in the EDC system according to the verification protocol to ensure the accuracy, completeness, and standardization of the data. If any entries into the eCRF are incorrect or incomplete, any discrepancies will be noted in the EDC system by means of electronic data queries. The CRA and data administrators will ask the investigator or CRC to make appropriate corrections. The corrected data will again be reviewed for completeness and consistency.

- 1. **Data review and cleaning**

Data cleaning methods includes EDC system automatic verification, SAS program cleaning, and manual verification. The investigator or CRC will confirm the questionable data on the basis of manual or systematic queries and make appropriate corrections. The monitor or data administrator will judge whether the data is reasonable according to the answers to questions, data updates, and audit tracks. If the data queries are still unresolved, they will be noted in the EDC system again until the queries solving and the data is clean.

- 1. **Electronic signature**

After the data entry was completed, all data queries were closed, and the monitoring staff checked and the data administrator checked, the investigator is responsible for verifying the authenticity and accuracy of the data reported in the EDC system and making an electronic signature in EDC. If there was any data modification after signature, it was necessary to sign again. The investigator must sign and date the Investigator’s Statement of electronic signature before any study-related procedures. It is required to declare that an electronic signature has the same legal effect as a written signature.

- 1. **Database locking**

The database locking will be confirmed after the completion of data entry, SDV, data queries clearance, electronic signature, SAE consistency check, medical verification, and data verification report. The data administrators will carry out the database locking after completing the listing procedure. The locked database will be not opened in principle.

- 1. **Data transfer**

To ensure the evaluation and supervision by the State Food and Drug Administration and sponsor, all documents must be archived by the research center and treated as confidential material, including confirmed documents (those that can effectively check different records, such as medical records), signed informed consent forms, and detailed source records of drug allocation. Data will be stored under lock and key for 5 years. The ownership of all documents will belong to Chia Tai Tianqing Pharmaceutical Group Co., Ltd. Investigator(s) shall not provide it to any third party in any form without the written consent of the sponsor, except for State Food and Drug Administration.

- 1. **Data preservation**

To ensure the evaluation and supervision by the State Food and Drug Administration and sponsor, all documents must be archived by the research center and treated as confidential material, including confirmed documents (those that can effectively check different records, such as medical records), signed informed consent forms, and detailed source records of drug allocation. Data will be stored under lock and key for 5 years. The ownership of all documents will belong to Chia Tai Tianqing Pharmaceutical Group Co., Ltd. Investigator(s) shall not provide it to any third party in any form without the written consent of the sponsor, except for State Food and Drug Administration.

1. **Statistical analysis management**
   1. **Analysis datasets**

- Full Analysis Set: According to the intention-to-treat (ITT) principle, the efficacy analysis was performed on all cases that received at least one dose of the drug.
- Per-protocol set (PPS): All randomized subjects who received at least 6 weeks of medication, had at least one imaging assessment, meeting the trial protocol, with favorable compliance, did not use prohibited drugs during the trial, and complete CRF. No imputation of missing data. Efficacy analysis was conducted based on both the FAS and PPS populations.
- Safety analysis set: All randomized subjects have received at least one dose of the research drug and have a post-administration safety record were included in the safety analysis set. This data set was used for the safety analysis.
  1. **Statistical Analysis Plans**

All statistical analyses were based on SAS version 9.4 or above. The quantitative variables were listed as mean, standard deviation, median, quartile, minimum and maximum values. Qualitative variables are listed as frequencies and percentages, with two decimal places reserved for percentages. The Kaplan-Meier method was used to analyze time-to-event data.

